### Incentive program preferences

To assess preference for incentive design, research staff describe two hypothetical financial incentive programs for smoking cessation, and then ask which program the participant prefers. One program uses goal-directed incentives (incentives weighted toward use of evidence-based therapies) and the other uses outcome-based incentives (incentives for successful achievement of an outcome such as successfully quitting) [5]. Total attainable incentives are similar in both programs. These data inform hypotheses regarding whether patients randomized to the incentive arm will demonstrate different smoking cessation outcomes depending on their prespecified (prerandomization) program preference.

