### Objectives

The primary objective of the Financial IncEntives for Smoking TreAtment (FIESTA) trial is to compare the effects of two approaches for smoking cessation—financial incentives plus enhanced usual care versus enhanced usual care alone—on smoking abstinence, use of evidenced-based therapy, and quality of life. The second objective is to estimate the short-term and long-term return on investment of using financial incentives to promote smoking cessation. In addition, the FIESTA Oral Microbiome Substudy will be conducted to determine whether smoking cessation changes the oral microbiome composition of smokers.

We hypothesize that participants in the financial incentives arm will experience higher rates of smoking cessation, improved quality of life, and lower rates of financial distress, and that these gains will be associated with a favorable return on investment. We also hypothesize that patients experiencing greater financial distress at baseline will be more likely to stop smoking in response to financial incentives. Our oral microbiome hypothesis is that smoking cessation will lead to changes in the microbiome that increase its similarity to the microbiome of nonsmokers.

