## Methods/design

### Overall design

The trial is sponsored by the Robert Wood Johnson Foundation. We will enroll 182 inpatient participants from the Manhattan campus of the Veterans Affairs (VA) New York Harbor Healthcare System. After conducting a baseline survey of the sociodemographic and clinical characteristics of participants and administering a Stages of Change questionnaire, smokers are randomized to the financial incentives plus enhanced usual care arm or the enhanced usual care alone arm with an allocation ratio of 1:1. All participants receive enhanced usual care, which includes tobacco use screening, counseling while hospitalized, hospital-directed educational materials on quitting smoking, nicotine replacement therapy (NRT) at the discretion of inpatient healthcare providers, and referral to a state Quitline (this component represents the enhancement). The components of enhanced usual care were selected based on prior evidence for effective smoking cessation interventions. In addition to enhanced usual care, smokers who are randomized to the financial incentives arm are also eligible to receive up to $550 for participating in counseling (both community-based counseling and state Quitline counseling), using smoking cessation pharmacotherapy, and biochemically confirmed smoking cessation at 2 months and 6 months. The incentive schedule is summarized in Table 1, and Figs. 1 and 2 display brochures provided to participants in the enhanced usual care arm or the financial incentives plus enhanced usual care arm.

**Table 1 Tab1:** Schedule of financial incentives

Activity	Time point	Incentive
Speaking with a coach from the NYS Smoker’s Quitline	2 weeks	$50
Completion of community-based smoking cessation program	2 weeks	$50
Use of pharmacotherapy for smoking cessation	2 weeks	$50
Smoking cessation (self-report + salivary cotinine)	2 months	$150
Smoking cessation (self-report + salivary cotinine)	6 months	$250

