### Randomization

Smokers are randomized in a 1:1 ratio to either financial incentives plus enhanced usual care or enhanced usual care alone. We employ a computer-generated block randomization design. Research staff implement the allocation sequence using numbered, sealed envelopes that are opened during participant enrollment. Because of the nature of the intervention, participants are not blind to their randomization into either the financial incentives plus enhanced usual care or enhanced usual care groups.

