### Data collection and measurement of smoking cessation outcomes

Participants are asked to complete an in-person survey at enrollment and four follow-up interviews by phone at 2 weeks, 2 months, 6 months, and 12 months. Each participant receives $20 after completing surveys at each of the follow-up time points. Each participant is also asked to provide saliva samples at enrollment and at 2 months, 6 months, and 12 months, for which we provide a $50 payment to increase participation rates. The baseline and follow-up surveys are similar in content and assess: 1) sociodemographic characteristics (i.e., demographics, contact information, race/ethnicity, health literacy, exercise habits, and nutrition habits) [24]; 2) smoking history (i.e., smoking habits and home environment using questions adapted from the California Tobacco Survey [25], nicotine dependence using questions adapted from the Heaviness of Smoking Index [26], and smoking cessation services received); 3) preference for incentive design (goal-directed versus outcome-based); 4) participant health (i.e., health status using the Veterans RAND 12-item Health Survey [27] and the EuroQol-5D [28–30] to assess physical and mental functioning, alcohol-use using the AUDIT-C [31, 32], marijuana use using the ASSIST, substance use using the self-administered Substance Use Brief Screen [33], and depression using the PHQ-2 [34]); and 5) health services utilization in the prior 6 months. The baseline and follow-up surveys also measure treatment outcomes (i.e., 7-day and 30-day point prevalence for smoking cessation, quit attempts, reduction in daily smoking, changes in readiness to quit, and use of NRT and Quitline counseling).

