### Analytic plan

The primary outcome in this trial is the smoking cessation rate at 6 months. Secondary outcomes in this trial include: 1) financial distress and security; 2) subjective social status; 3) other substance use including alcohol; and 4) quality of life. Chi-squared tests, *t* tests, and nonparametric tests will be used to compare baseline characteristics of patients to assess balance between the two study arms. Multivariate analyses for longitudinal data will include difference-in-difference models and Cox proportional hazard models, and these models will include patient-level variables, area-based socioeconomic factors, and hospital variables as covariates.

For the economic evaluation, we will estimate the return on investment of financial incentives intervention from the perspective of the healthcare system (hospitalizations, ambulatory care, and medications) on a per-patient basis. Costs will be determined by: 1) multiplying employee wages (based on United States Bureau of Labor Statistics values) [35] by the estimated time these personnel spend on smoking cessation care; 2) using the Red Book to estimate NRT and other medication costs (based on average wholesale prices) [36]; and 3) estimating bulk purchase prices for other physical materials provided to smokers. The return on investment will then be estimated using the difference between the value of financial incentives provided to smokers and the incremental healthcare costs or savings, comparing the financial incentives plus enhanced usual care arm to the enhanced usual care alone arm.

We will also estimate the cost-effectiveness of the financial incentives intervention using the ratio of the difference in costs between the intervention group and control group to the difference in quality of life and smoking cessation rates between the intervention and control groups [37]. We will perform nonparametric bootstrapping with 1000 random samples to estimate confidence intervals (CIs) for the cost-effectiveness ratios and we will use the bias-corrected percentile method described by Efron and others [38–40]. We will consider recidivism rates of participants when estimating the cost-effectiveness of the interventions in this trial. Specifically, we anticipate that recidivism will reduce cost-effectiveness by reducing the incremental benefits of the intervention.

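### The incentive-preference question is framed as a contrast within the incentive arm, which mixes prognosis with response to incentives; the control arm already holds the data that would separate them

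*Protocol article*

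**What the plan says.** Under Incentive program preferences, "research staff describe two hypothetical financial incentive programs for smoking cessation, and then ask which program the participant prefers". One programme weights payment towards use of treatment, the other towards quitting itself. The section then states the purpose: to inform hypotheses about "whether patients randomized to the incentive arm will demonstrate different smoking cessation outcomes depending on their prespecified (prerandomization) program preference". The group named is the incentive arm. No comparison with control patients of the same preference is mentioned.

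Three other places show that control patients supply the same information:

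- Data collection and measurement of smoking cessation outcomes lists incentive-design preference as the third content area of the surveys, and says "Participants are asked to complete an in-person survey at enrollment", without restriction by arm.
- Overall design fixes the order: "After conducting a baseline survey of the sociodemographic and clinical characteristics of participants and administering a Stages of Change questionnaire, smokers are randomized" to one of the two arms.
- Randomization gives the allocation: "Smokers are randomized in a 1:1 ratio".

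The Analytic plan section does not mention preference, either as an outcome or as a model term.

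**The concern.** Patients sort themselves into preference groups. Those who would rather be paid for quitting may, for example, be more confident or less dependent, and may quit more often in either arm. If quit rates are compared by preference among incentive patients, that prognostic difference appears in the result together with any real difference in response.

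The error can go either way. A purely prognostic preference could be read as a sign that some patients respond better to incentives, and a real difference in response could be hidden by an opposite prognostic difference. Nothing inside the incentive arm helps to separate the two, because Table 1 gives every incentive patient the same schedule: 3 × $50 = $150 for treatment steps and $150 + $250 = $400 for confirmed cessation, $550 in all.

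**Working it through.** **Inputs from the article.** 91 patients per arm, a 20-point difference of interest, α = 0.05 and 10–15% loss at 6 months (Sample size); allocation 1:1 (Randomization). The article gives no figure for the preference question and no quit rate by preference, so there is no stated result to reproduce on this point.

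**Assumptions.** All preference-specific quit rates below, an even split of preferences, and a two-sided test (sidedness is not stated).

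**Step 1: what the within-arm contrast estimates.** Let C1, C2 be the control quit rates and I1, I2 the incentive quit rates in preference groups 1 and 2. Then

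I2 − I1 = (C2 − C1) + [(I2 − C2) − (I1 − C1)].

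The first term is prognosis. The bracket is the difference in incentive effect. Without C1 and C2 the two cannot be told apart.

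**Step 2: numbers.**

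| Assumed case | Control, groups 1 / 2 | Incentive, groups 1 / 2 | Incentive effect, groups 1 / 2 | Within-incentive gap | Difference in effect |
|---|---|---|---|---|---|
| Simple example | 15% / 25% | 35% / 45% | 20 / 20 | 10 | 0 |
| A: prognosis only | 10% / 30% | 30% / 50% | 20 / 20 | 20 | 0 |
| B: response differs, masked | 30% / 10% | 40% / 40% | 10 / 30 | 0 | 20 |
| C: response differs, no prognosis | 20% / 20% | 30% / 50% | 10 / 30 | 20 | 20 |

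Cases A and C have identical incentive arms (30% and 50%) and opposite answers. Only the control arm distinguishes them.

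**Step 3: how often each test would reject, 91 per arm, 45.5 per cell.**

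- Case A, within-arm two-proportion test: about 50% (43% after 15% loss), although the difference in effect is zero. The arm-by-preference test rejects at its nominal 5%.
- Case B, within-arm test: nothing beyond its 5% error rate. Arm-by-preference test: the standard error is √[(0.21 + 0.24 + 0.09 + 0.24)/45.5] = √(0.78/45.5) = 0.131, so z = 0.20/0.131 = 1.53 and power is about 33% (29% after 15% loss; about 30% with a 70/30 preference split and no loss).

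**Step 4: the price in precision.** With equal groups, the ratio of the interaction standard error to the within-arm standard error is √[(Vc + Vi)/Vi], where V is the sum of p(1 − p) over the two preference groups in an arm.

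- Simple example: Vc = 0.15 × 0.85 + 0.25 × 0.75 = 0.315 and Vi = 0.35 × 0.65 + 0.45 × 0.55 = 0.475, so the ratio is √(0.790/0.475) = 1.29.
- If the two arms had equal variances, the ratio would be √2 = 1.41.

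**Step 5: what the trial could detect.** With overall rates of 20% and 40%, the difference in effect detectable with 80% power is (1.96 + 0.84) × √[2 × (0.16 + 0.24)/45.5] = 2.80 × 0.133, about 37 points (about 40 after 15% loss).

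**Step 6: scale.** The zero in the simple example holds for risk differences. On the odds scale, the ratio between preference groups is (0.25/0.75)/(0.15/0.85) = 1.89 in control and (0.45/0.55)/(0.35/0.65) = 1.52 under incentives, an interaction odds ratio of about 0.80. The scale therefore has to be named in advance.

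**The case against.** The strongest reply is that the article commits to no analysis here. It speaks of informing hypotheses, names no test, model or comparison group, and leaves preference out of the Analytic plan. A full protocol or analysis plan, not shown, could specify an interaction. This stands in part: a reader might infer that the trial will analyse the incentive arm only, but the text does not exclude a control comparison and could loosely be read as effect modification. What remains is the framing. The one sentence that defines the question names a one-arm contrast.

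Second, asking who quits under an incentive programme is a legitimate descriptive question, and a within-arm comparison answers it. That also stands, provided the result is not then called response to incentives.

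Third, a reader might infer that the trial intends to conclude that matching incentive design to preference improves quitting. The section makes no such claim, and with one schedule for everyone in the arm the trial could not test it.

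Fourth, a reader might extend the point to the hypothesis in Objectives that "patients experiencing greater financial distress at baseline will be more likely to stop smoking in response to financial incentives". That wording already asks about response to incentives and restricts nothing to one arm. It is not an error.

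Finally, the better analysis has low power (Step 3). That is true, but a more precise estimate of a mixed quantity does not answer the question about response.

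**Conclusion.** The point holds as a minor one, confined to the wording under Incentive program preferences. As framed, the contrast supports a descriptive association among incentive patients and cannot show that preference changes the response to incentives. The algebra needs no assumed rates. The sizes do: a 10-point gap with no difference in effect in the simple example, and about a 50% chance of a significant within-arm result in case A, both with invented rates and evenly split preferences.

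The primary analysis is not affected. "The primary outcome in this trial is the smoking cessation rate at 6 months", and preference is neither a listed secondary outcome nor part of the sample size. It would be wrong to infer from this point that the main comparison, or the financial-distress hypothesis, is flawed.

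**What to change.** Reword the sentence under Incentive program preferences so that preference stated before randomisation is examined as an effect modifier in all randomised patients. Report the incentive-minus-control risk difference in 6-month cessation within each preference group, and the difference between those two risk differences with a 95% CI. State that the scale is the risk difference and that the analysis is exploratory. If a comparison within the incentive arm is also shown, describe it as descriptive only. Preference remains a self-selected marker, so even a clear interaction would show who responds, not that preference is the cause.

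The change costs one sentence and needs no new data, patients or procedures. The estimate is less precise, with a standard error roughly 1.3 to 1.4 times that of the within-arm contrast under the assumed rates, and only very large differences in effect would be detectable. The exploratory label and the confidence interval make that plain.

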### Adverse events

At all scheduled contact between staff and participants, patients are asked about any potential adverse events that had occurred since enrollment or their most recent follow-up assessment. This list of potential events includes violations of confidentiality, emergency room visits without hospitalization, and suicidal ideation not requiring intervention, as well as serious adverse events, including death, life-threatening events, hospitalization, and suicidal ideation requiring intervention. If a patient experiences an adverse event, staff record: 1) event onset date; 2) report date; 3) reporting staff member; 4) study phase, i.e., prerandomization, in-treatment, or follow-up; and 5) a detailed description of the adverse event, i.e., symptoms, course, duration, treatment, or cause of death if known.

### Data monitoring

The study coordinators generate reports for the principal investigators on a monthly basis. These reports contain a summary of enrollment, retention, participant withdrawals, detailed descriptions of adverse events, and detailed descriptions of protocol violations. Reports are periodically submitted to the Institutional Review Board (IRB) for continued review. The principal investigators are notified within 24 h of recognition of any adverse events. Serious adverse events are reported within 10 business days to the IRB.

### Sample size

We will enroll 182 smokers and expect a 60% participation rate. In addition, we expect a 10–15% loss to follow-up rate at 6 months. We consider an absolute difference of approximately 20% in smoking cessation rates to be clinically substantial, where absolute difference = (rate_1_ – rate_2_). Therefore, this sample size (91 patients per arm) allows at least 80% power to detect a substantial clinical difference in smoking cessation rates between the control group (enhanced usual care alone arm) and intervention group (financial incentives plus enhanced usual care arm) with α = 0.05.

### Analytic plan

The primary outcome in this trial is the smoking cessation rate at 6 months. Secondary outcomes in this trial include: 1) financial distress and security; 2) subjective social status; 3) other substance use including alcohol; and 4) quality of life. Chi-squared tests, *t* tests, and nonparametric tests will be used to compare baseline characteristics of patients to assess balance between the two study arms. Multivariate analyses for longitudinal data will include difference-in-difference models and Cox proportional hazard models, and these models will include patient-level variables, area-based socioeconomic factors, and hospital variables as covariates.

For the economic evaluation, we will estimate the return on investment of financial incentives intervention from the perspective of the healthcare system (hospitalizations, ambulatory care, and medications) on a per-patient basis. Costs will be determined by: 1) multiplying employee wages (based on United States Bureau of Labor Statistics values) [35] by the estimated time these personnel spend on smoking cessation care; 2) using the Red Book to estimate NRT and other medication costs (based on average wholesale prices) [36]; and 3) estimating bulk purchase prices for other physical materials provided to smokers. The return on investment will then be estimated using the difference between the value of financial incentives provided to smokers and the incremental healthcare costs or savings, comparing the financial incentives plus enhanced usual care arm to the enhanced usual care alone arm.

We will also estimate the cost-effectiveness of the financial incentives intervention using the ratio of the difference in costs between the intervention group and control group to the difference in quality of life and smoking cessation rates between the intervention and control groups [37]. We will perform nonparametric bootstrapping with 1000 random samples to estimate confidence intervals (CIs) for the cost-effectiveness ratios and we will use the bias-corrected percentile method described by Efron and others [38–40]. We will consider recidivism rates of participants when estimating the cost-effectiveness of the interventions in this trial. Specifically, we anticipate that recidivism will reduce cost-effectiveness by reducing the incremental benefits of the intervention.

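### Difference-in-difference models, if used as is natural for the secondary scores, give up precision that adjusting for the baseline score would keep

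*Protocol article*

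**What the plan says.** The Analytic plan section of the protocol article states that the multivariate longitudinal analyses "will include difference-in-difference models"; Cox models are named beside them. It adds that "these models will include patient-level variables, area-based socioeconomic factors, and hospital variables as covariates". It does not name the baseline value of the outcome among those covariates, and it does not say which outcome goes with which model.

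The same section lists the secondary outcomes as "1) financial distress and security; 2) subjective social status; 3) other substance use including alcohol; and 4) quality of life".

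The section on data collection and measurement of smoking cessation outcomes sets the timing: "Participants are asked to complete an in-person survey at enrollment and four follow-up interviews by phone". The first of these interviews is at 2 weeks and the last at 12 months, with two between them, at months 2 and 6. Of the questionnaires it says "The baseline and follow-up surveys are similar in content and assess", among other things, "health status using the Veterans RAND 12-item Health Survey [27] and the EuroQol-5D [28–30] to assess physical and mental functioning", with alcohol use measured by the AUDIT-C. The Randomization section gives 1:1 random allocation.

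**The concern.** Difference-in-difference removes a systematic baseline difference between groups. Randomisation already makes that difference zero on average, so there is nothing systematic to remove. The method then reduces to an arm comparison of change from baseline. It subtracts the whole baseline score, although only the part that predicts the follow-up score is useful. The rest is added noise.

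What is at stake is the width of the intervals and the power for the secondary scores. Quality of life matters most, because the Objectives section includes it in the primary objective. The sample size was set for cessation alone, so there is no stated margin of precision for these scores.

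**Working it through.** **Which outcomes are concerned.** Under Eligibility criteria, every trial participant smoked in the 30 days before admission, so cessation has essentially no baseline variation to difference. Cox models are for time to an event. That leaves repeated survey measures. VR-12, EQ-5D and AUDIT-C are documented at baseline and follow-up. Baseline financial distress is implied by a hypothesis under Objectives. For subjective social status no baseline measurement is described.

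**The plan's own figure.** The article gives no power or precision for any secondary outcome. Its one power statement (at least 80%, 91 per arm, a 20-point difference in cessation, α = 0.05) concerns the primary outcome. It cannot be reproduced from the stated inputs because no control rate is given. If 20% versus 40% is assumed, two-sided, the continuity-corrected size is 91 per arm. Nothing below changes that statement.

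**Inputs.**
- Patients per arm with data: 91 × 0.85 = 77.35, about 77 (Sample size section, upper end of the expected 10–15% loss at 6 months).
- Two-sided α = 0.05 (sidedness assumed).
- Correlation ρ between baseline and follow-up score: not stated; range 0.3 to 0.9 assumed.
- SDs at baseline (s0) and follow-up (s1): not stated; assumed equal for the sizes, but not for the direction.

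**Direction.** For one follow-up visit, the per-patient variances are:
- change score: s0² + s1² − 2ρ·s0·s1
- baseline-adjusted (ANCOVA), large sample: s1²(1 − ρ²)
- gap: s0² − 2ρ·s0·s1 + ρ²·s1² = (s0 − ρ·s1)², which is never negative.

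So difference-in-difference cannot be more precise than baseline adjustment, whatever ρ and the SDs are.

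**Size, with equal SDs.** In units of the follow-up variance, follow-up only = 1, change score = 2(1 − ρ), baseline-adjusted = 1 − ρ². The ratio of change score to adjusted is 2/(1 + ρ). The difference detectable with 80% power is (1.96 + 0.84) × √(2/77.35) × √(variance factor), in SD units; with follow-up only it is 0.45. The last column is the power of difference-in-difference at the effect for which baseline adjustment has 80%.

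| ρ | Change score | Adjusted | Ratio | Detectable, change score | Detectable, adjusted | Power |
|---|---|---|---|---|---|---|
| 0.3 | 1.40 | 0.91 | 1.54 | 0.53 | 0.43 | 62% |
| 0.5 | 1.00 | 0.75 | 1.33 | 0.45 | 0.39 | 68% |
| 0.7 | 0.60 | 0.51 | 1.18 | 0.35 | 0.32 | 73% |
| 0.9 | 0.20 | 0.19 | 1.05 | 0.20 | 0.20 | 78% |

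The change-score variance exceeds 1 when 2(1 − ρ) > 1, that is, when ρ < 0.5. There, difference-in-difference is noisier than ignoring baseline. Put another way, 2 × 77 = 154 completers analysed by change score give the precision of about 154 × (1 + ρ)/2 = 100, 116 and 131 analysed with baseline adjustment, at ρ = 0.3, 0.5 and 0.7.

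**Check by simulation** (8000 trials, 77 per arm). Standard errors for follow-up only, difference-in-difference and adjusted were 0.162, 0.190, 0.155 at ρ = 0.3; 0.163, 0.161, 0.141 at 0.5; and 0.162, 0.124, 0.115 at 0.7. These agree with the formulas.

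**The case against.** The strongest objection is that the article does not commit to an unadjusted change-score analysis of these outcomes. The list of models is not exhaustive, and no outcome is assigned to one. The baseline score is a patient-level variable, so the covariate clause could cover it. A change-score model that includes it gives exactly the ANCOVA estimate for the arm effect, and the loss disappears. A condensed article may also leave the covariate list to a fuller document.

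Part of this stands. The link to the secondary scores is an inference, and the covariate reading is possible. But the text does not state that reading. It would also not help if covariates enter a stacked model of baseline and follow-up records as main effects only: with complete data, time-invariant covariates then leave the difference-in-difference estimate unchanged. The point is about a method the article names, not about a detail it omits.

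A reader might infer more than the documents support:
- *That the estimate is biased, or that chance baseline imbalance enters in full.* Under randomisation the method is unbiased. With a chance imbalance d and equal SDs, the expected follow-up imbalance is ρd. Subtracting d leaves −(1 − ρ)d, which is 0.7d, 0.5d and 0.3d in size at ρ = 0.3, 0.5 and 0.7.
- *That ρ is known to be low* because baseline is taken in hospital and follow-up by phone after discharge. That is plausible for quality of life, but the article gives no figure.
- *That the cost-effectiveness ratio is weakened.* The article does not say that its quality-of-life difference comes from the difference-in-difference model.
- *That every secondary outcome is affected.* A baseline value is not documented for social status, and the variance formulas are only approximate for short screening instruments.

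**Conclusion.** The point holds as a loss of efficiency on those secondary scores that have a baseline measurement. The direction follows from randomisation alone. The size rests on an unstated ρ and on equal SDs: 54%, 33%, 18% and 5% more variance at ρ = 0.3, 0.5, 0.7 and 0.9. It is therefore substantial at low to moderate correlation and negligible at high correlation. The ρ = 0.5 threshold for being worse than ignoring baseline also depends on equal SDs. The application to these scores is inferred, though it is the natural reading. Validity is not in question, and the power for the primary outcome is unaffected.

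**What to change.** For each secondary score with a baseline measurement, replace difference-in-difference with a longitudinal model of the follow-up scores that has the baseline value as covariate (or a baseline mean constrained to be common to both arms) and arm-by-visit terms. Report the adjusted arm differences at 6 and 12 months. State which outcomes this covers, and confirm for each, social status in particular, that a baseline value is collected.

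The cost is a few sentences in the analysis plan. Where the baseline score exists, no further data or patients are needed.

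### The bias-corrected bootstrap interval is unreliable for the quality-of-life cost-effectiveness ratio, because the trial is not sized to keep that denominator away from zero

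*Protocol article*

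**What the plan says.** The economic part of the Analytic plan (protocol article) contains two separate analyses. Return on investment comes first and is defined as a difference between money amounts. Cost-effectiveness follows as a ratio, in which the cost difference between arms is set in proportion "to the difference in quality of life and smoking cessation rates between the intervention and control groups". For its uncertainty the article states: "We will perform nonparametric bootstrapping with 1000 random samples to estimate confidence intervals (CIs) for the cost-effectiveness ratios", and it names the bias-corrected percentile method for the limits. It gives no rule for resamples in which the effect difference is zero or negative.

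The Sample size section deals with cessation only: "We consider an absolute difference of approximately 20% in smoking cessation rates to be clinically substantial", and "this sample size (91 patients per arm) allows at least 80% power" for that difference, "with α = 0.05". It also says "we expect a 10–15% loss to follow-up rate at 6 months". The data collection section lists the VR-12 and the EQ-5D as quality-of-life instruments. No SD, expected difference or power is given for either.

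**The concern.** A ratio is discontinuous where its denominator passes through zero. With a positive cost difference, an effect just above zero gives a very large positive ratio and an effect just below zero a very large negative one, although the two resamples are almost the same. A negative ratio can also mean cheaper and better or dearer and worse. Percentile limits require the resamples to be ranked from favourable to unfavourable, and once signs mix that ranking no longer exists.

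The bias correction adds a second problem. It measures bias by the share of resampled ratios that lie below the estimate. Sign flips change that share for reasons unrelated to bias, and the limits then move.

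The article's own expectations bring the situation closer. It hopes for a favourable return on investment, so the cost difference may be negative too, and it anticipates that relapse will shrink the incremental benefit. What is at stake is the confidence interval of the quality-of-life ratio and, if the effect falls short of design, that of the cessation ratio.

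**Working it through.** **Inputs from the article.** 91 per arm; 1:1 allocation; 10–15% loss, so 91 × 0.90 ≈ 82 and 91 × 0.85 ≈ 77 remain; a 20-point cessation difference; α = 0.05 (taken as two-sided); 1000 resamples; bias-corrected percentile limits.

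**The plan's own figure.** For 20% against 40%, two-sided 0.05 and 80% power, the two-proportion formula with continuity correction gives exactly 91 per arm. The control rate is not stated. Without the correction, 91 per arm gives 88%, 84% and 81% power at control rates of 15%, 20% and 25%. The size is therefore reproducible for cessation and has no bearing on quality of life.

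**How often the quality-of-life denominator crosses zero.** Working in SD units avoids assuming an SD. The standard error of the difference is √(2/n): 0.148 at 91 per arm and 0.161 at 77. Resamples centre on the observed difference, so at least 2.5% are ≤ 0 when that difference is below 1.96 SE. For a true difference d, the chance is Φ(1.96 − d/SE). At 0.1 SD and 91 per arm, Φ(1.96 − 0.67) = 0.90.

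The coverage columns come from simulation: 1500 trials of 1000 resamples, normal quality of life, and lognormal costs independent of effect (mean 3000, SD 300 or 3000, cost difference 300; all assumed).

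| True difference | Chance that ≥ 2.5% of resamples are ≤ 0 (91; 77 per arm) | Coverage, bias-corrected ratio interval | Coverage, net benefit, same resamples |
|---|---|---|---|
| 0.1 SD | 90%; 91% | 63–74% | 93–95% |
| 0.2 SD | 73%; 76% | 80–86% | 93–95% |
| 0.42 SD | 19%; 26% | 94–96% | 93–95% |

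To hold that chance at 20% needs d = (1.96 + 0.84) × SE: 0.415 SD at 91 per arm and 0.452 SD at 77. If incentives improve quality of life only through 20 points more quitters, each extra quitter would have to gain 0.415/0.20 ≈ 2.1 SD to 0.452/0.20 ≈ 2.3 SD.

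**On an assumed EQ-5D scale.** With SD 0.2 and 77 per arm, SE = 0.2 × 0.161 = 0.032. Simulations under several cost assumptions gave bias-corrected coverage of about 55–63% at a true difference of 0.01 (single runs as low as 51%) and 78–84% at 0.04. The plain percentile interval covered 89–99% in these runs.

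**Why the two intervals differ.** Suppose the observed effect is 1 SE below zero and the cost difference is fixed and positive.
- The estimated ratio is negative, and the 34% of resamples with an effect between −1 SE and 0 have a smaller ratio. So z₀ = Φ⁻¹(0.341) = −0.41.
- The bias-corrected upper limit is then the Φ(2 × −0.41 + 1.96) = Φ(1.14) ≈ 87th percentile, not the 97.5th.
- The top 12.7% of ratios are cut off. They come from effects between 0 and about 0.85 SE, since Φ(1.85) = 0.841 + 0.127. With SE 0.032 that is 0 to about 0.027, so a true effect of 0.01 is excluded.
- The plain interval cuts only 2.5%, from effects between 0 and about 0.11 SE (about 0.0035), and keeps the truth. It does so by spanning ratios of both signs.

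At a true difference of 0.01, the point estimate is itself ≤ 0 in Φ(−0.01/0.032) ≈ 38% of trials.

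**Cessation ratio.** With the unpooled binomial SE and a true 20-point difference, the chance that at least 2.5% of resamples are ≤ 0 is 6–21% (91 per arm) or 11–28% (77 per arm) for control rates of 10–40%. Simulated coverage at a 15% control rate is 94–97%. At a true 10-point difference the chance is 52–76% and coverage about 84–89%.

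**The case against.** The strongest reply is that this is a supplementary analysis and that the failure depends on inputs the article does not give. Several stronger conclusions that a reader might infer are indeed unsupported.

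- *Crossing is near certain for quality of life.* Without an SD or expected difference in the article, this cannot be said. At 0.42 SD material crossing is a minority event and coverage is nominal.
- *The main economic result is invalid.* Return on investment leads the economic plan and is the second objective. As a difference it has no effect denominator, so the problem does not reach it. Nor does it reach the primary cessation result.
- *Every ratio interval fails.* The cessation ratio behaves acceptably at the effect the trial was designed for.
- *Percentile ordering in itself destroys coverage.* The loss is specific to the bias correction. The plain percentile interval stays near nominal.

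What survives is narrower. The bias-corrected method is the one the article specifies, so this is a stated choice and not a detail left to an analysis plan. It performs poorly over a plausible range of quality-of-life effects. Changing to the plain percentile interval would restore most of the coverage, but its limits would be just as uninterpretable when signs mix.

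**Conclusion.** The point holds for the quality-of-life ratio and, conditionally, for the cessation ratio. At the stated size, the quality-of-life difference is kept clear of zero only if it is about 0.4 SD or more. Below that, material crossing is probable (about 90% at 0.1 SD, about 75% at 0.2 SD), and the specified interval covers well under 95%. The crossing probabilities rest on the article's sample size and a normal approximation. The coverage figures rest also on assumed costs and, on the EQ-5D scale, an assumed SD of 0.2. The cessation interval needs attention only if the true effect falls well short of 20 points. This should be changed before analysis, but it concerns a secondary economic analysis and leaves the trial's main conclusions untouched.

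**What to change.** Keep the bootstrap and its 1000 cost-effect pairs. Base inference on incremental net monetary benefit (willingness to pay × effect difference − cost difference) with a 95% CI over a prespecified range of willingness-to-pay values, for both quality of life and cessation. Add the cost-effectiveness plane or an acceptability curve. Report the quality-of-life ratio as a point estimate, without a bias-corrected percentile interval. From the same resamples, net benefit covered 93–97% in the simulations.

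Do not adopt a rule that prints a ratio interval only when no resample crosses zero. It would make reporting depend on the data, and it would often suppress the cessation interval at the design effect, where that interval is sound.

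The cost is a few lines of code and wording, with no new data. The one real demand is that the willingness-to-pay values, per unit of quality of life and per quitter, must be chosen and justified in advance.
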